**Dummy Tables**

**Table 1: Demographic and Clinical characteristics of the participants**

| **S. No.** | **Characteristic** | **Experimental group**  **(n=43)** | **Control group**  **(n=43)** | **Test Statistics** |
| --- | --- | --- | --- | --- |
|  | Age (years) *Mean+SD* |  |  | t:p = |
|  | Time since stroke (months) *Mean+SD* |  |  | t:p = |
|  | Male/female - *n (%)* |  |  | χ^2^:p = |
|  | Socio-economic status (BPL/LIG/MIG/HIG) - *n (%)* |  |  | χ^2^:p = |
|  | Educational qualification (years)  *Mean+SD* |  |  | t:p = |
|  | Marital status (married/unmarried/widowed) - *n (%)* |  |  | χ^2^:p = |
|  | Ischemic/Hemorrhagic - *n (%)* |  |  | χ^2^:p = |
|  | Area of involvement (Frontal/parietal/frontoparietal/internal capsule/ basal ganglia/thalamus/ multiple/others) - *n (%)* |  |  | χ^2^:p = |
|  | Risk factors – *n (%)* |  |  | χ^2^:p = |
|  | 1. Hypertension - *n (%)* 2. Smoking - *n (%)* 3. Alcoholic - *n (%)* 4. Tobacco Use - *n (%)* 5. Hereditary - *n (%)* 6. Diabetes mellitus - *n (%)* 7. Obesity- *n (%)* 8. Pregnancy - *n (%)* 9. Coronary artery disease - *n (%)* 10. Peripheral vascular disease - *n (%)* 11. Dyslipidemia- *n (%)* 12. Previous Stroke - *n (%)* |  |  | χ^2^:p =  χ^2^:p =  χ^2^:p =  χ^2^:p =  χ^2^:p =  χ^2^:p =  χ^2^:p =  χ^2^:p =  χ^2^:p =  χ^2^:p =  χ^2^:p =  χ^2^:p = |
|  | Side of involvement (Right/left) – *n (%)* |  |  | χ^2^:p = |
|  | Dominant side (Right/left) – *n (%)* |  |  | χ^2^:p = |
|  | BRS-U (Stage1/2/3/4/5/6) – *n (%)* |  |  | χ^2^:p = |
|  | BRS-H (Stage 1/2/3/4/5/6) – *n (%)* |  |  | χ^2^:p = |
|  | BRS-L (Stage 1/2/3/4/5/6) – *n (%)* |  |  | χ^2^:p = |
|  | Shoulder subluxation (Grade 1/2/3) – *n (%)* |  |  | χ^2^:p = |
|  | Shoulder support– *n (%)* |  |  | χ^2^:p = |
|  | Hand Splint– *n (%)* |  |  | χ^2^:p = |
|  | MAS (0/1/1+/2) – *n (%)*   1. Shoulder adductors 2. Elbow flexors 3. Forearm pronators 4. Wrist flexors |  |  | χ^2^:p =  χ^2^:p =  χ^2^:p =  χ^2^:p = |
|  | Walking devices (walker/quadripod/stick) – *n (%)* |  |  | χ^2^:p = |
|  | AFO (hinged/non-hinged) – *n (%)* |  |  | χ^2^:p = |
|  | Pain (VAS)   1. Shoulder *(Median; IQR)* 2. Wrist *(Median; IQR)* 3. Hand *(Median; IQR)* |  |  | U:p=  U:p=  U:p= |
|  | Cognitive impairment (mild/moderate) *- n (%)* |  |  | χ^2^:p = |
|  | Psychosocial behavior (depression/aggression) - *n (%)* |  |  | χ^2^:p = |
|  | Speech (Expressive aphasia/dysarthria) - *n (%)* |  |  | χ^2^:p = |
|  | Language impairment (writing/reading) - *n (%)* |  |  | χ^2^:p = |

BPL: Below poverty line, LIG: Lower income group, MIG: Middle income group, HIG: Higher income group, UG: Under graduate, PG: Post graduate, BRS-U: Brunnstrom recovery stage of arm, BRS- H: Brunnstrom recovery stage of hand, BRS- L: Brunnstrom recovery stage of lower limb SD: Standard deviation , MAS- Modified ashworth scale, IQR – Inter quartile range, AFO-Ankle foot orthosis, VAS – Visual analog Scale

**Table 2: Changes in Pre- and Post-intervention, and Follow-up scores of the Letter Cancellation Task (LCT) between the experimental and control groups**

| **Outcome measure** | **Pre-intervention** | | **Post-intervention (8-week)** | | **Follow-up (12-week)** | |  | | |
| --- | --- | --- | --- | --- | --- | --- | --- | --- | --- |
|  | **Experimental Group (n=43)** | **Control Group (n=43)** | **Experimental Group (n=43)** | **Control**  **Group (n=43)** | **Experimental Group (n=43)** | **Control**  **Group (n=43)** | **Difference between the means**  **(95% CI)** | **F** | **P value** |
| **LCT (Right)**  *Mean*±*SD*  *Maximum score = 20* |  |  |  |  |  |  |  |  |  |
| **LCT (Left)**  *Mean*±*SD*  *Maximum score = 20* |  |  |  |  |  |  |  |  |  |

n – Number, SD – standard deviation, CI - confidence interval, F – test value ANOVA

**Table 3: Changes in Pre- and Post-intervention, and Follow-up scores of the Line Bisection Test (LBT) between the experimental and control groups**

| **Outcome measure** | **Pre-intervention** | | **Post-intervention (8-week)** | | **Follow-up (12-week)** | |  | | |
| --- | --- | --- | --- | --- | --- | --- | --- | --- | --- |
|  | **Experimental Group (n=43)** | **Control Group (n=43)** | **Experimental Group (n=43)** | **Control**  **Group (n=43)** | **Experimental Group (n=43)** | **Control**  **Group (n=43)** | **Difference between the means**  **(95% CI)** | **F** | **P value** |
| **LBT (Right)**  *Mean*±*SD*  *Maximum score = 20* |  |  |  |  |  |  |  |  |  |

n – Number, SD – standard deviation, CI - confidence interval, F – test value ANOVA

**Table 4: Changes in Pre- and Post-intervention, and Follow-up scores of the Fugl-Meyer Assessment (FMA) between the experimental and control groups**

| **Outcome measure** | **Pre-intervention** | | **Post-intervention (8-week)** | | **Follow-up (12-week)** | |  | | |
| --- | --- | --- | --- | --- | --- | --- | --- | --- | --- |
|  | **Experimental Group (n=43)** | **Control Group (n=43)** | **Experimental Group (n=43)** | **Control**  **Group (n=43)** | **Experimental Group (n=43)** | **Control**  **Group (n=43)** | **Difference between the means**  **(95% CI)** | **F** | **P value** |
| **FMA**  *Mean*±*SD*  *Maximum score = 100* |  |  |  |  |  |  |  |  |  |
| **FMA-UE**  *Mean*±*SD*  *Maximum score = 66* |  |  |  |  |  |  |  |  |  |
| **FMA-UA**  *Mean*±*SD*  *Maximum score =36* |  |  |  |  |  |  |  |  |  |
| **FMA-WH**  *Mean*±*SD*  *Maximum score =30* |  |  |  |  |  |  |  |  |  |
| **FMA-LE**  *Mean*±*SD*  *Maximum score = 34* |  |  |  |  |  |  |  |  |  |

n – Number, SD – standard deviation, CI - confidence interval, F – test value ANOVA, UE-upper extremity, UA-upper arm, WH-wrist-hand, LE – Lower extremity

**Table 5: Changes in Pre- and Post-intervention, and Follow-up scores of the Catherine Bergego Scale (CBS) between the experimental and control groups**

| **Outcome measure** | **Pre-intervention** | **Post-intervention (8-week)** | **Follow-up (12-week)** | | | |  | | |
| --- | --- | --- | --- | --- | --- | --- | --- | --- | --- |
|  | **Experimental Group (n=43)** | **Control Group (n=43)** | **Experimental Group (n=43)** | **Control**  **Group (n=43)** | **Experimental Group (n=43)** | **Control**  **Group (n=43)** | **Difference between the means**  **(95% CI)** | **F** | **P value** |
| **CBS**  *Mean*±*SD*  *Maximum score =30* |  |  |  |  |  |  |  |  |  |

n – Number, SD – standard deviation, CI - confidence interval, F – test value ANOVA

**Table 6: Changes in Pre- and Post-intervention, and Follow-up scores of the Berg Balance Scale (BBS) between the experimental and control groups**

| **Outcome measure** | **Pre-intervention** | | **Post-intervention (8-week)** | | **Follow-up (12-week)** | |  | | |
| --- | --- | --- | --- | --- | --- | --- | --- | --- | --- |
|  | **Experimental Group (n=43)** | **Control Group (n=43)** | **Experimental Group (n=43)** | **Control**  **Group (n=43)** | **Experimental Group (n=43)** | **Control**  **Group (n=43)** | **Difference between the means**  **(95% CI)** | **F** | **P value** |
| **BBS** *Mean*±*SD*  *Maximum score =56* |  |  |  |  |  |  |  |  |  |

n – Number, SD – standard deviation, CI - confidence interval, F – test value ANOVA

**Table 7: Changes in Pre- and Post-intervention, and Follow up scores of the Functional Ambulation Category (FAC) between the experimental and control groups**

| **Outcome measure** | **Pre-intervention** | |  | **Post-intervention** | |  | **Follow-up** | | |
| --- | --- | --- | --- | --- | --- | --- | --- | --- | --- |
|  | **Experimental Group (n=43)** | **Control Group (n=43)** | **Test**  **Statistics** | **Experimental Group (n=43)** | **Control**  **Group (n=43)** | **Test**  **Statistics** | **Experimental Group (n=43)** | **Control**  **Group (n=43)** | **Test**  **Statistics** |
| FAC 0 *– n (%)* |  |  | χ^2^:p = |  |  | χ^2^:p = |  |  | χ^2^:p = |
| FAC 1*– n (%)* |  |  |  |  |  |  |  |  |  |
| FAC 2*– n (%)* |  |  |  |  |  |  |  |  |  |
| FAC 3*– n (%)* |  |  |  |  |  |  |  |  |  |
| FAC 4*– n (%)* |  |  |  |  |  |  |  |  |  |
| FAC 5*– n (%)* |  |  |  |  |  |  |  |  |  |

n – Number

**Table 8: Changes in Pre- and Post-intervention, and Follow up scores of Modified Rankin Scale (mRS) between the experimental and control groups**

| **Outcome measure** | **Pre-intervention** | |  | **Post-intervention** | |  | **Follow-up** | | |
| --- | --- | --- | --- | --- | --- | --- | --- | --- | --- |
|  | **Experimental Group (n=43)** | **Control Group (n=43)** | **Test**  **Statistics** | **Experimental Group (n=43)** | **Control**  **Group (n=43)** | **Test**  **Statistics** | **Experimental Group (n=43)** | **Control**  **Group (n=43)** | **Test**  **Statistics** |
| mRS 0 *– n (%)* |  |  | χ^2^:p = |  |  | χ^2^:p = |  |  | χ^2^:p = |
| mRS 1*– n (%)* |  |  |  |  |  |  |  |  |  |
| mRS 2*– n (%)* |  |  |  |  |  |  |  |  |  |
| mRS 3*– n (%)* |  |  |  |  |  |  |  |  |  |
| mRS 4*– n (%)* |  |  |  |  |  |  |  |  |  |
| mRS 5*– n (%)* |  |  |  |  |  |  |  |  |  |

n – Number

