**Secondary objectives**

- 1. To determine the effectiveness of the Task-based and Magnified mirror therapy on functional performance of the subjects
  2. To determine the effectiveness of the protocol on disability status among the subjects.

1. **Methodology:**

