**Secondary measures**

- - 1. ***Catherine Bergego Scale***

The Catherine Bergego Scale (CBS) is used to measure neglect. It is a valid, reliable, and sensitive measure of poststroke neglect. Specifically, it has good internal consistency, inter-rater reliability, concurrent validity and convergent validity. The CBS is a functional neglect assessment because it assesses neglect through observation of activities such as eating and locomotion (i.e. collisions, navigation items). The CBS has items that assess for personal, peripersonal, and extrapersonal neglect and the type of neglect each item assesses has been delineated. Assessors score 10 items using a 4-point scale. Higher CBS scores (range: 0-30) indicate more severe neglect. Kessler Foundation Neglect assessment Process guidelines will be used to apply the CBS.[^47^](#_ENREF_47)^,^ [^48^](#_ENREF_48)

- - 1. ***Berg Balance Scale***

The Berg Balance Scale (BBS) has been developed to measure balance among older people with impairment in balance function by assessing the performance of functional tasks. It is a valid instrument used for evaluation of the effectiveness of interventions and for quantitative descriptions of function in clinical practice and research.[^49^](#_ENREF_49) It is a commonly used measure to assess balance ability among post-stroke subjects.[^50^](#_ENREF_50) It is a 14-item measure, items ranging from sit-to-stand to standing on one foot. All the items are score on 0 to 4, 4 being the positive performance. The total score is 56, with < 40 and < 20 being considered as medium and high fall risk, respectively for the subject.

- - 1. ***Functional Ambulation Category (FAC)***

Functional Ambulation Category (FAC) measures the walking ability of the poststroke subjects. It is an economical and simple method to quantify independency in ambulation. The scale defines 6 categories ranging from 0 (unable to walk) to 5 (independent walking). FAC has exhibited acceptable reliability and validity.[^51^](#_ENREF_51)^,^ [^52^](#_ENREF_52)

- - 1. ***Modified Rankin scale***

The modified Rankin scale (mRS) is a clinician-reported and recommended measure of global disability.[^53^](#_ENREF_53) It is widely used for evaluating trial outcomes of stroke patients and is an end point in randomized clinical trials.[^54^](#_ENREF_54) mRS scores range from 0 (no symptoms at all) to 5 (severe disability)

*Distribution of Outcome measure as per International classification of Functioning (ICF)*

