**Data Analysis:**

The data will be analyzed by using IBM SPSS version 23.0. The demographic and baseline features of the study participants will be analyzed in form of mean (SD) / median (IQR) / n (%) and appropriate test [(Mann-Whitney U (U) / independent t (t) / chi-square (χ^2^)] tests will be used to analyze the difference for the characteristics between the groups. For inferential statistics, an intention-to-treat analysis method will be used by carrying forward the last observation. A repeated-measures 2-way ANOVA (continuous data; within factor, time; between factor, group) will be used to study difference for the post intervention and follow-up scores between the groups. The pre-intervention score will be considered as the covariate with group as the independent variable and posttest score as the dependent variable. The significance level will be set at *P*<.05. The dummy tables to represent the findings are provided below -

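### FAC and mRS are ordered scales, but Tables 7 and 8 test them with a chi-square per visit that ignores category order and baseline and loses a substantial part of the power

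*Protocol*

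**What the plan says.** Under Secondary measures, the protocol describes FAC as graded: "The scale defines 6 categories ranging from 0 (unable to walk) to 5 (independent walking"). It describes the mRS in the same way: "mRS scores range from 0 (no symptoms at all) to 5 (severe disability"). The mRS is the only instrument that the outcome table classes as disability. It therefore carries the second secondary objective, "To determine the effectiveness of the protocol on disability status among the subjects". FAC is the only ambulation measure.

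Dummy Tables 7 ("Follow up scores of the Functional Ambulation Category (FAC) between the experimental and control groups") and 8 ("Follow up scores of Modified Rankin Scale (mRS) between the experimental and control groups") list six levels as n (%) by arm. Each visit (pre-intervention, post-intervention and follow-up) has one test-statistic column holding a single chi-square p-value. Neither table has a column for a difference, an odds ratio or a confidence interval.

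The Data Analysis section does not supply another outcome test for these scales. Its longitudinal model is limited to continuous outcomes: "A repeated-measures 2-way ANOVA (continuous data; within factor, time; between factor, group"). The baseline-adjustment sentence follows directly: "The pre-intervention score will be considered as the covariate with group as the independent variable and posttest score as the dependent variable". Mann-Whitney is named only in the sentence on demographic and baseline features, whose "tests will be used to analyze the difference for the characteristics between the groups".

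**The concern.** A Pearson chi-square on a two-by-six table treats the levels as labels. Shuffling the six rows would leave the p-value unchanged. The test asks whether the two distributions differ in any way and spends 5 degrees of freedom on it. The clinical question is whether one arm is shifted towards better ambulation or less disability, which needs 1 degree of freedom.

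Three further points follow from the layout.

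- A contingency-table chi-square takes no covariate. The baseline level goes unused, although the Data Analysis section intends baseline adjustment for the outcomes it models.
- No effect size with an interval is reported, so a reader gets a p-value and percentages but no estimate of benefit.
- The pre-intervention chi-square tests only whether randomisation produced a chance imbalance and says nothing about treatment.

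At stake are the whole of the disability objective and part of the functional one.

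**Working it through.** **The plan's own figure.** None exists for these scales. The only power calculation concerns the Line Bisection Test (37 per group, raised to 43).

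**Inputs from the protocol.** Six levels per scale; 43 per arm as printed in the table headings; 1:1 allocation; alpha 0.05, taken as two-sided.

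**Inputs assumed.** Control distribution 10/15/25/25/15/10%; a proportional-odds shift with marginal odds ratio (OR) of 2, 2.5 or 3; latent baseline-outcome correlation of 0.5 to 0.7.

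**Step 1: degrees of freedom.** (2 − 1) × (6 − 1) = 5 if every level is filled, and 3 if only four are.

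**Step 2: cost of ignoring order, analytically.** Hold the noncentrality where a 1-df test has 80% power: (1.96 + 0.84)² ≈ 7.85. A 5-df chi-square with that noncentrality has 55.5% power, and a 3-df one has 64.5%. To reach 80% the noncentrality must rise to 12.83 (5 df) or 10.90 (3 df). The sample-size ratios are 12.83/7.85 = 1.63 and 10.90/7.85 = 1.39.

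**Step 3: simulation under the assumed inputs.** The adjusted test regresses outcome ranks on group and baseline ranks.

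| Marginal OR | Chi-square | Mann-Whitney | Baseline-adjusted rank test |
|---|---|---|---|
| 2 | about 21% | about 42% | 52-64% |
| 2.5 | about 37% | about 65% | 75-87% |
| 3 | about 54% | about 82% | 89-97% |

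With no effect, all three tests reject at close to 5%.

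Share of power lost by chi-square against Mann-Whitney (order alone):
- OR 2: (42 − 21)/42 = 50%
- OR 2.5: (65 − 37)/65 = 43%
- OR 3: (82 − 54)/82 = 34%

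Share lost against the adjusted test (order and baseline):
- OR 2: (52 − 21)/52 = 60% to (64 − 21)/64 = 67%
- OR 2.5: (75 − 37)/75 = 51% to (87 − 37)/87 = 57%
- OR 3: (89 − 54)/89 = 39% to (97 − 54)/97 = 44%

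**Step 4: sensitivity.**
- Three other assumed six-level distributions, correlation 0.7: at OR 2, chi-square 20-23%, Mann-Whitney 41-45%, adjusted 60-68%. At OR 3, 51-55%, 76-82% and 93-96%.
- Four occupied levels: at OR 2, 28%, 42% and 61%. At OR 3, 62%, 78% and 94%.
- OR defined conditionally on baseline, correlation 0.7: at OR 2, 11%, 22% and 39%. At OR 2.5, 18%, 37% and 60%. At OR 3, 27%, 51% and 73%.

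Absolute power depends heavily on the type of odds ratio. The ranking of the three tests never changes.

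**Step 5: sparse cells.** With equal arms, an expected count is half the level's total, so it falls below 5 when the level holds fewer than 10 patients. One such level gives 2 of 12 cells (17%) and two give 4 of 12 (33%). Two thin levels are therefore enough to pass the usual 20% mark. At the assumed control proportions each end level averages 86 × 0.10 = 8.6 patients. In about half of the simulated tables more than 20% of expected counts were below 5.

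**The case against.** **The chi-square stands only in dummy tables, and a separate analysis plan may say more.** The tables nevertheless name a specific test for each visit, and the Data Analysis text offers no other outcome test for these scales. This is a stated choice rather than a detail left open. The tables do not say which chi-square is meant. The ordinary Pearson test is an inference, but the natural one, since no trend version is named.

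**A reader might infer that most of the power is lost and that a real shift would usually be missed.** The documents do not support that as a general statement. They give no expected effect, distribution or correlation for FAC or mRS. Against the adjusted test, more than half is lost at marginal odds ratios of 2 and 2.5, or when the odds ratio is conditional on baseline. At a marginal odds ratio of 3 the loss is under half, and chi-square detects the shift slightly more often than not.

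**A reader might also infer that a significant result could not show which arm did better.** It could, informally: the n (%) columns by arm stand beside the p-value. What is missing is a summary estimate with an interval.

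**Scope is limited.** These are two of four secondary measures, and no power is claimed for them. The functional objective also draws on the Catherine Bergego and Berg scales, which go through the ANOVA. This limits the importance of the point but does not remove it, because the disability objective has no other measure.

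**The remedy meets the same sparsity.** That is fair if baseline enters as a six-level factor, which can cost up to 5 df with 86 patients. Entering it as a score costs 1 df.

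**Conclusion.** The point holds in measured form. For two scales that the protocol itself describes as graded, the only outcome test shown ignores the grading and the collected baseline, and no effect estimate is planned. That much follows from the test and the table layout and needs no assumption beyond reading chi-square as the Pearson test.

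The size does rest on assumptions. For marginal odds ratios of 2 to 3, ignoring order alone costs about a third to a half of the Mann-Whitney power. Ignoring baseline as well brings the loss to about 39-67% of what an adjusted test would have. A substantial part of the power is the supportable wording. The change is well worth making, but it concerns secondary outcomes and does not touch the primary analysis or the sample size.

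**What to change.** In the Data Analysis section, add a sentence that FAC and mRS will each be analysed at week 8 and at week 12 by a proportional-odds (ordinal logistic) model, with group and the baseline level entered as a score (1 df). The common odds ratio will be reported with its 95% CI. Name rank ANCOVA or Mann-Whitney as the fallback if levels are too sparse or proportional odds clearly fails.

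In Tables 7 and 8, keep the n (%) rows, replace the post-intervention and follow-up chi-square columns with the odds ratio, interval and p-value, and remove the pre-intervention test.

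The cost is one sentence, new table columns and a brief check of the proportional-odds assumption. SPSS, already the planned software, fits the model through its PLUM procedure. Data collection, visits and sample size stay as they are.

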**Data management:**

Data from clinical assessments will be recorded in paper booklets for each patient and converted with double data entry into a PC data file stored on a secured server of the site of study. A copy of data will also be stored in a secured pen drive on weekly basis. A data code sheet will be developed, giving a unique code to each information and numerical scoring system for each of them. The data will be entered into Excel spread sheet before the analysis by the SPSS software. The entry will be done on completion of each subject’s pre or post assessment. Random check of the entered data will be conducted by the principal investigator. Participants’ paper files will be kept for storage for a period of 5 years and electronic data will be stored on a secured server. Confidential information will be converted into unique codes and the key to these codes will be kept in a separate file on a password protected electronic location.

**Ethical Consideration:**

For this study, the approval will be sought from the Institutional ethics committee (IEC) of *Pt. Deendayal Upadhya National Institute for Persons with Physical Disabilities, New Delhi, India.* The trial will comply with the principles of the “declaration of Helsinki.” Before the start of participation in this study, written informed consent will be obtained. All data collected during this study will be confidential but with open access for investigators / research staff at the study site. To protect the privacy of the participants, they will be given unique numerical codes. The key to this code will be maintained securely and confidentially by the principal Investigator. No information with which the participant can be identified will be available in any other study-related (electronic) document. All assessment forms, reports, and other (electronic) records will be coded and handled to maintain strict participant confidentiality.

The participants may withdraw from the study at any time without giving an explanation and without any negative consequences for their care or rehabilitation in the future. Based on our previous studies,[^24^](#_ENREF_24)^,^ [^34^](#_ENREF_34)^,^ [^35^](#_ENREF_35) the judgment is that there is no or very low risk of adverse events in this proposed investigation. If any adverse event is observed during the protocol, the same will be reported to the IEC and described in the dissemination of the work.

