USN is a strong predictor of poor motor recovery and functional performances among the stroke subjects.[^12^](#_ENREF_12) The impaired ability has significant physical, social, and emotional implications. Considering the International Classification of Functioning, Disability and Health, USN undoubtedly affects body structure and function that subsequently leads to activity limitation and participation restriction.

Cognitive rehabilitation has been recommended as one of the important areas of stroke research that warrant independent synthesis of evidence generated in LMICs.[^13^](#_ENREF_13) Further, globally, research on cognitive impairment after stroke is at an earlier stage of evolution than research in motor recovery.[^14^](#_ENREF_14) The studies to enhance cognitive deficits among stroke survivor are recommended as a top first question for research.[^15^](#_ENREF_15) The proposed study may be applicable to the *National Stroke Registry Program (NSRP) / National Programme for Prevention and Control of Cancer, Diabetes, Cardiovascular Diseases and Stroke* (NPCDCS) in terms of rehabilitation services to control and prevent disability for comprehensive management of stroke patients.[^16^](#_ENREF_16)^,^ [^17^](#_ENREF_17)

[^15^](#_ENREF_15)

1. **Literature review:**

USN is a frequent and disabling impairment after stroke. The terms unilateral neglect, visuospatial neglect, hemineglect and spatial neglect are used interchangeably. Although the USN usually occurs on the contralesional side in the right brain damage, the deficit may be observed on the ipsilesional side as well as among subjects with the left brain damage.[^11^](#_ENREF_11)^,^ [^18^](#_ENREF_18)^,^ [^19^](#_ENREF_19) The functional performance of an individual with USN gets hampered. Most of the investigations have been focused on the impairment and management of upper limb functions. In addition to this, the USN affects lower limb functions such as locomotion and stair climbing. The post-stroke subjects with USN are at more risk of falling in comparison to the subjects without USN.[^20^](#_ENREF_20)^,^ [^21^](#_ENREF_21) The functional ambulation including stair climbing gets more impaired than the stroke subjects without USN.[^20^](#_ENREF_20)^,^ [^22^](#_ENREF_22) Further, USN has been identified as a key element that may impede upper limb and lower limb recovery.[^12^](#_ENREF_12)

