***Rationale:*** Cognitive deficits are a major cause of disability in post- stroke subjects. Spatial neglect has visual, perceptual, and motor factors. Post-stroke with USN exhibited poor functional outcome when compared with individuals without USN. The presence of USN is associated with poor upper limb motor control, both at subacute and chronic stages.[^12^](#_ENREF_12) A range of therapeutic approaches comprising cognitive and behavioral approaches has been applied in visuospatial neglect. However, there is no consensus as to which rehabilitation method is most effective.[^23^](#_ENREF_23) There is very limited evidence that cognitive rehabilitation may have an immediate beneficial effect on neglect. Further, there is a lack of investigations and insufficient evidence related to upper limb therapies in post-stroke subject with USN. This justifies the need for further clinical trials of cognitive rehabilitation for neglect.[^11^](#_ENREF_11) The investigations on USN using mirror therapy have either been conducted on acute subjects or underestimating the importance of motor outcome. The common neurobiological mechanism for proportional recovery rule[^33^](#_ENREF_33) both for the upper limb and USN demands the intervention of dual action. In addition to the upper limb, the USN also affects the motor and functional performance of the lower limb. However, no USN rehabilitation techniques have incorporated the lower limb aspect. The other crucial knowledge gaps in this context are: use of magnified vision for USN and use of mirror in the parasagital plane for USN. It is understood that appropriate and comprehensive intervention for USN would not only reduce the cognitive disability but also induce substantial motor and functional recovery.

1. **Novelty:**

The proposed study would be the first investigation to utilize the tasks for providing the mirror therapy among stroke subjects with USN. The meaningful tasks induce movements that appear out of an interaction between multiple brain areas to manipulate a real-world object. Such movements increase the cortical activity and may reduce greater the deficit than the movements without task.[^34^](#_ENREF_34)

Apart from the upper limb, the activity-based mirror therapy protocol[^35^](#_ENREF_35) will also be provided for the lower limb to comprehensively reduce the impact of USN. This would be the first study to incorporate the lower limbs in any USN rehabilitation study.

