Magnifying the image of a body part (hand or arm), has a positive and beneficial effect on activity performance and thus motor recovery among stroke subjects.[^32^](#_ENREF_32)^,^ [^36^](#_ENREF_36) Mirror therapy providing image without magnification has been utilized in management of USN. No cognitive rehabilitation protocol utilizing magnified image of the neglected body part has been investigated yet. The proposed study would be the first investigation of magnified mirror for creating illusion for the affected upper limb by the less-affected side. When the vision of the limb will be magnified, the illusion may induce enlargement of the cortical representation of the body part. Thus, enhancing the underlying neuromechanism[^25^](#_ENREF_25) of mirror therapy.

The fourth novelty of this proposed investigation is the use of mirror therapy to provide visual feedback for the affected limb (upper or lower limb) in the parasagital plane. Although it has been suggested by the developers of the mirror therapy[^30^](#_ENREF_30), no mirror-based rehabilitation trials has applied the concept of visual feedback for USN.

Further, the present study will also be focused on management of USN among chronic stroke[^37^](#_ENREF_37), unlike the previous investigations.

1. **Study objectives**:

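### Adverse events are captured only passively and no scheduled enquiry about falls or pain is specified, so the protocol's low-risk judgment cannot be tested reliably

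*Protocol*

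**What the plan says.** The protocol's only text on harms is in Ethical Consideration. Relying on three earlier trials by the same team, it states that "the judgment is that there is no or very low risk of adverse events in this proposed investigation". The capture rule follows: "If any adverse event is observed during the protocol, the same will be reported to the IEC and described in the dissemination of the work". It gives no definition of an adverse event, no scheduled question, no log and no capture period.

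Other parts of the protocol bear on this:

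- **Literature review:** "The post-stroke subjects with USN are at more risk of falling in comparison to the subjects without USN".
- **Secondary measures, Berg Balance Scale:** "The total score is 56, with < 40 and < 20 being considered as medium and high fall risk, respectively for the subject".
- **SPIRIT schedule:** rows for the seven outcome measures and for baseline characteristics; none for adverse events or falls.
- **Dummy Table 1:** shoulder, wrist and hand pain on a visual analogue scale, at baseline only. Tables 2 to 8 cover the efficacy measures.
- **Novelty:** "No cognitive rehabilitation protocol utilizing magnified image of the neglected body part has been investigated yet", and, on the lower-limb component, "This would be the first study to incorporate the lower limbs in any USN rehabilitation study". The same section also presents task-based mirror therapy in neglect, and parasagittal visual feedback among mirror-based trials, as new.
- **Data management:** entry is tied to each participant's pre- or post-assessment. No route is described for events that occur between assessments.

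**The concern.** A rule that starts from observation depends on someone seeing an event or being told of it. The protocol identifies falling as a raised hazard in this population, and both arms include physical activity, yet no one is instructed to ask about falls. New or worse limb pain, another foreseeable event in hemiparetic patients doing repeated tasks, has a baseline value and no planned later value to compare with it.

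Two things are at stake. First, a report of few or no events could mean that few occurred or that few were noticed, and the reader could not tell which. Second, the therapists deliver the treatment and so know the arm. What they notice, prompt for or write down may differ between arms, and an uneven count could mislead in either direction.

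This cannot be left to an analysis plan. How harms are ascertained decides which data exist, and no later analysis can recover events that nobody asked about.

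**Working it through.** The protocol gives no adverse-event or fall rate, so there is no figure of its own to reproduce. The check has three parts.

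**1. Where could a harm enter the data?**

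| Place in the protocol | Route for a fall or new pain |
| --- | --- |
| Ethical Consideration | Yes, if observed |
| SPIRIT schedule, T2 and T3 | No row |
| Outcome measures | Berg bands grade balance; the Catherine Bergego Scale observes collisions during activities; neither counts falls |
| Dummy Table 1 | Pain at baseline only |
| Dummy Tables 2 to 8 | None |
| Data management | Entry after assessments; no between-visit route described |

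The one open route is the passive one.

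**2. What would systematic enquiry buy?** Inputs are 43 per arm and 86 in total (Sample size). If all n participants are asked and none has an event, the exact upper 95% limit for the per-patient risk is 1 − 0.05^(1/n) one-sided and 1 − 0.025^(1/n) two-sided.

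- n = 43: 1 − 0.05^(1/43) = 6.7%; 1 − 0.025^(1/43) = 8.2%.
- n = 86: 1 − 0.05^(1/86) = 3.4%; 1 − 0.025^(1/86) = 4.2%.

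The chance of seeing at least one event among 86 with full capture is 1 − (1 − p)^86. For assumed per-patient risks p of 1%, 2%, 5% and 10% this is 58%, 82%, 99% and nearly 100%. So with everyone asked, the trial could examine a low-risk statement at about the 3 to 4% level overall and 7 to 8% per arm.

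These limits require complete capture. If only a fraction c of affected participants is recorded, zero recorded events bounds c × p rather than p. As an illustration with assumed values, c = 0.5 turns the one-sided limit for 86 into 3.42% / 0.5 = 6.8%, and c = 0.25 turns it into 3.42% / 0.25 = 13.7%. Under the passive rule c is unknown, so no limit can be stated.

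**3. How far do the cited trials carry the risk judgment?** Under Experimental Intervention, the upper-limb component follows one of the three cited trials, modified for neglect, and the lower-limb component follows another. Each takes 20 minutes, so together they fill 20 + 20 = 40 of the 60 experimental minutes. The remaining 20 minutes are magnified mirror therapy (10) and parasagittal feedback (10). By their titles in the reference list, the cited trials concern sensori-motor, upper-limb motor and lower-limb motor and gait recovery after stroke. Novelty presents all four components as new in neglect. The support is therefore real for technique and limited for this population and package.

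**The case against.** The case for leaving the text alone has force in several places.

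- **A reader might infer that falls are not collected at all.** The documents do not support that. A fall known to staff is an adverse event under the stated rule, must go to the ethics committee and must be described in publication. The Annexure I proforma is cited but not shown. What can be said is that no systematic collection is specified.
- **A reader might infer that only treating therapists notice events, and only during sessions.** The rule names neither an observer nor a place. Participants may volunteer events, and the assessor, who is unaware of allocation, sees them at T2 and T3.
- **A reader might take the small share of clock time under supervision as the share of events caught.** It is not. Participants attend five days a week for eight weeks, so a fall at home could well be mentioned at the next session. The gap is likely wider in the last four weeks. The flow diagram lists four weeks of conventional rehabilitation there, as I read its order, but gives no session frequency.
- **A reader might see a contradiction between the raised fall risk and the low-risk judgment.** There is none. The first compares patients with and without neglect; the second concerns taking part in this trial. Both can be true.
- **A reader might hope that better capture would show whether the programme changes falls.** With 43 per arm it would not. For an assumed 15% against 30% of participants falling, the standard error is √[(0.15 × 0.85 + 0.30 × 0.70)/43] = 0.0886, and power is Φ(0.15/0.0886 − 1.96) = Φ(−0.27), about 39% (38% with the pooled variance under the null).
- **The risk judgment has some basis.** The upper-limb tasks are done seated and the lower-limb frames are for short and long sitting. The Literature review also cites a 48-patient mirror-therapy trial in neglect, pilot work with a parasagittal mirror, and magnified vision in 25 chronic stroke patients.

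All of these points stand, and they limit the concern. None of them supplies a scheduled question, and without one an absence of reports is not evidence of an absence of events. The layout of a harms table could be left to an analysis plan; the decision to ask cannot.

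**Conclusion.** The concern holds as a gap in ascertainment. Harms are captured passively, falls are named as a hazard but not asked about, and pain has no planned value after baseline. The resulting count may be incomplete and may differ by arm because therapists know the allocation. Observed events will be published, so the low-risk judgment can be examined in part, but it cannot be tested reliably. With every participant asked, zero events would bound per-patient risk at 3.4% overall and 6.7% per arm (one-sided 95%); the present rule supports no bound. The cited trials support the judgment in part, and the rest is extrapolation.

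This rests on the text shown. If the unseen annexures hold fixed questions on falls and adverse events at follow-up, the gap narrows to their absence from the schedule. The size of any undercount is unknown, and the capture fractions and risks used above are assumptions. No efficacy conclusion depends on the point. It is a worthwhile and inexpensive improvement to what the trial can say about safety.

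**What to change.** Make these changes in Ethical Consideration and carry them into the schedule:

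1. Replace passive capture with the same fixed questions in both arms at T2 and T3: falls, injury, new or worse pain, and other events since the last assessment.
2. Note events volunteered at sessions on the attendance record, in both arms.
3. Repeat the baseline shoulder, wrist and hand pain scale at T2 and T3.
4. Add rows for these items to the SPIRIT schedule.
5. Report counts by arm through week 12 descriptively, with no test of a between-arm difference in falls.
6. Qualify the risk sentence: the judgment is partly extrapolated from trials that did not study this package in patients with neglect.

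Reporting to the ethics committee stays as it is.

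The cost is protocol wording, a short question sheet and a few minutes at visits already planned. More minor events will be reported than under the present rule. There is also a small risk that answers reveal the arm to the assessor; asking after the outcome tests are finished, and telling participants not to describe their therapy, limits it.
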